### Randomization, allocation concealment and blinding

The Brightech Clinical Information Management System (CIMS) will be used for central randomization, which is performed by Brightech Clinical Medicine Research Co. Ltd. in Chengdu, China. Only authorized research assistants can obtain random numbers and group assignment information by logging into the CIMS website, which can ensure the randomization will not be influenced by researchers and patients. The randomization information will be concealed in the server until the end of the trial.

It is not possible to blind acupuncturists in this trial, therefore, they will not take part in the assessment procedure. Participants in different groups will receive treatment in different therapeutic rooms and be blinded to their treatment allocations. After all the treatment sessions, they will be asked to guess what kind of acupuncture treatment they have received (acupuncture or superficial acupuncture). Outcome assessors and statisticians will be blinded to the treatment allocation.

### Interventions

Combining Chinese acupuncture experts’ opinions with the results from data mining analysis of acupoints, a standardized acupoints prescription consisting of *Fengchi* (GB20), *Baihui* (GV20), *Taiyang* (EX-HN5), *Hegu* (LI4), and *Taichong* (LR3) will be applied for CTTH treatment in this trial (Table 1). Participants in both groups will receive 20 sessions of acupuncture over 8 weeks (three sessions per week in the first 4 weeks and two sessions per week in the last 4 weeks). Acupuncturists who have at least 5 years of professional training will receive training classes before this trial. Contents of the training include acupoint locating, needle manipulation skills, and communication skills. The acupuncturists can participate in the trial if they pass the trial training examination.

**Table 1 Tab1:** Details of acupuncture and superficial acupuncture treatment

Group	Acupoints	Manipulation
Acupuncture	*Fengchi* (GB20)	0.5–0.8 *cun* (12.5–20 mm) oblique insertion towards the tip of the nose.
	*Baihui* (GV20)	0.5–0.8 *cun* (12.5–20 mm) subcutaneous insertion.
	*Taiyang* (EX-HN5)	0.3–0.5 *cun* (7.5–12.5 mm) perpendicular insertion.
	*Hegu* (LI4)	0.5–0.8 *cun* (12.5–20 mm) perpendicular insertion.
	*Taichong* (LR3)	0.5–0.8 *cun* (12.5–20 mm) perpendicular insertion.
		Retaining needles for 30 min. Lifting, thrusting, twisting and/or rotating the needles twice every 10 min with intermittent stimulation for maintaining the *deqi* sensation.
Superficial acupuncture	*Fengchi* (GB20)	Controlling depth within 2 mm by inserting needles with limited tubes, and retaining needles for 30 min without any manipulation to avoid *deqi* sensation as far as possible.
	*Baihui* (GV20)	
	*Taiyang* (EX-HN5)	
	*Hegu* (LI4)	
	*Taichong* (LR3)	

#### Acupuncture treatment group

All acupoints will be punctured by filiform needles (sterile, disposable needles provided by Suzhou Hwato Medical Instruments Co. Ltd., Suzhou, China) when patients are in a comfortable sitting position. The needles of 25 to 45 mm in length and 0.25 mm in diameter will be inserted into the acupoints and the depths will be adjusted to the standard permissible layers of each acupoint. Then an even reinforcing-reducing technique, which means lifting, thrusting, twisting, and rotating the needles moderately, will be performed on the needles until achieving the *deqi* sensation. The needles will be retained for 30 minutes in each session and manipulated every 10 minutes with intermittent stimulation for maintaining the *deqi* sensation. The manipulation of each acupoint will last for 10 seconds.

#### Superficial acupuncture control group

Participants in the control group will receive superficial acupuncture using filiform needles on the same acupoints as the treatment group. The depth of penetration into the skin will be controlled to within 2 mm by limited tubes, and the needles will be retained for 30 minutes without any manipulation to avoid the *deqi* sensation as much as possible.

### Outcome measurements

The following outcomes will be assessed by independent assessors blinded to the allocation.

#### Primary outcome

The primary outcome measurement is the proportion of responders at week 16. A responder is defined as a participant with a decrease of at least 50% less headache days during 4 weeks. A participant with a reduction of less than 50% headache days, including anyone with missing data, is defined as a nonresponder. This outcome measurement will be assessed at week 16 after randomization.

#### Secondary outcome

The secondary outcome measurements are (1) number of headache days per 4 weeks, (2) the mean intensity of headache recorded by visual analogue scale score and grade of headache intensity per 4 weeks, (3) the reduction of medication intake per 4 weeks, (4) the 36-item short form health survey (SF-36) [20], (5) Hamilton Depression Scale (HAMD) [21] and Hamilton Anxiety Scale (HAMA) [22] results, (6) number of participants with adverse events (AEs) and serious adverse events (SAEs), (7) expectation values of acupuncture treatment, (8) the intensity of the *deqi* sensation.

All participants will be asked to complete a daily headache dairy and return them to assessors by emails, short messages or telephone calls throughout the whole 36-week observation period. The first three secondary outcomes will be extracted from the headache diaries. And the three outcomes followed will be assessed at each visiting time point. All of the above outcome measurements will be assessed at baseline, and at 4, 8, 12, 16, 20, 24, 28, and 32 weeks after randomization. Moreover, the expectation value of acupuncture treatment will be collected at baseline and week 8 after randomization, and the intensity of the *deqi* sensation will be assessed at 5 minutes after each treatment using the Massachusetts General Hospital Acupuncture Sensation Scale (MASS).

Details of AEs and SAEs will be documented during the 36-week period, such as occurrence time, duration, coping methods, and the correlation with treatment. AEs include bleeding, hematoma, fainting, severe pain, local infection, and so on, while SAEs are defined as life-threatening events, leading to significant or persisted disability, resulting in or prolonging hospitalization.

Researchers responsible for recruiting participants and assessors responsible for collecting data must receive training to ensure all of them have the same standards and understand the purpose, contents, and quality control of the trial. Detailed time points of outcome assessments are provided in Fig. 2.

### Data collecting and monitoring

Data will be recorded on the paper version of case report forms (CRFs) by designated outcome assessors, and double entered in the electronic CRFs, which is established and monitored by the Evidence-based Medicine Center of Chengdu University of Traditional Chinese Medicine. Monitors will audit the data every 3 months. Acupuncturists and statisticians will have no access to these data during the evaluating process.

### Statistical analysis

Primary analysis will be based on intention-to-treat population, including participants with at least one assessment of the primary outcome and one acupuncture session. Per protocol (PP) analysis will be performed to test the robustness of the primary analysis. PP population will include participants receiving at least 12 sessions of acupuncture and be assessed at week 8 and 16.

The primary outcome will be analyzed with a random intercept logistic regression model, taking treatment allocation as a random factor and taking sex, age, and duration of headache as fixed factors. The secondary outcomes (headache days, headache intensity, SF-36, HAMA, HAMD results) will be analyzed using a generalized least squares regression model, with the same covariates as the primary outcome. For the rest of outcomes, we will make pairwise comparisons using a general linear model adjusted for baseline value, age, sex, and disease course. Missing values of the primary outcome will be imputed by the last-observation-carried-forward method. We will run several sensitivity analysis to ensure the robustness of the imputation: first, lost-to-follow-up participants in the acupuncture group will be recognized as nonresponders, whereas those in the superficial acupuncture group will be recognized as responders; second, lost-to-follow-up participants will be counted as responders in the acupuncture group but nonresponders in the superficial group; Third, all lost-to-follow-up participants will be treated as nonresponders. Missing values in the secondary outcomes will be imputed by using the multiple imputation method (*n* = 5).

All confidence intervals will be two-sided 95% intervals comparing acupuncture to superficial acupuncture and all statistical hypotheses will be two-sided tests. Analyses will be performed using the R and Stata programs.

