**Design:**

A two-armed, parallel-design, patient-assessor blind, randomized controlled trial is underway in China. A total of 218 participants with CTTH will be randomly assigned to the treatment group or the control group in a 1:1 ratio. Participants in the treatment group and control group will receive acupuncture or superficial acupuncture treatments in a fixed prescription of acupoints respectively, for a total of 20 sessions over 8 weeks. The posttreatment follow-up period will be 24 weeks. The primary outcome will be the proportion of responders assessed at week 16 after randomization. The secondary outcomes will include the number of headache days, the mean intensity of headache, the reduction of medication intake, results from the 36-item short form health survey, the Hamilton Depression Scale and the Hamilton Anxiety Scale, the number of participants with adverse events, the expectation value of acupuncture treatment, and the intensity of *deqi* sensation. The first five secondary outcomes will be assessed or calculated at baseline, and at 4, 8, 12, 16, 20, 24, 28, and 32 weeks after randomization. Moreover, the expectation value will be collected at baseline and at week 8 after randomization, the intensity of *deqi* sensation will be assessed at 5 minutes after each treatment and adverse events will be summarized at the end of the follow-up period.

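### The set labelled intention-to-treat depends on post-randomisation data and, as worded, cannot be reconciled with a single week-16 outcome and its missing-data rules

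*Protocol article*

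**What the plan says.** The Statistical analysis section defines the primary analysis set as the "intention-to-treat population, including participants with at least one assessment of the primary outcome and one acupuncture session".

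The outcome itself has one time point. The Primary outcome section states: "This outcome measurement will be assessed at week 16 after randomization". The abstract agrees: "The primary outcome will be the proportion of responders assessed at week 16 after randomization". Responder status is defined for no other week.

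The article then gives several rules for a missing primary outcome:

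- Primary outcome section: a participant with too small a reduction, "including anyone with missing data, is defined as a nonresponder".
- Statistical analysis section: "Missing values of the primary outcome will be imputed by the last-observation-carried-forward method".
- Same section, first sensitivity analysis: "lost-to-follow-up participants in the acupuncture group will be recognized as nonresponders, whereas those in the superficial acupuncture group will be recognized as responders".
- Same section, second sensitivity analysis: "lost-to-follow-up participants will be counted as responders in the acupuncture group but nonresponders in the superficial group".
- Same section, third sensitivity analysis: everyone lost is a nonresponder.

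The Dropout criteria section adds that participants who withdraw, or who do not reach 12 sessions, are removed. It does not say whether that means from treatment, from follow-up or from the analysis.

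**The concern.** An intention-to-treat set keeps every randomised participant in the assigned arm. This set admits participants only if they had a session and gave outcome data, and both happen after allocation. The arms differ by design in needle depth, manipulation and sought sensation, and the acupuncturists know the allocation. Early loss could therefore differ between arms, and the comparison would lose part of the protection of randomisation.

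The second problem is internal consistency. The missing-data rules exist for participants whose week-16 status is unknown. If the set admits only those whose status is known, the planned robustness checks must agree with the primary result whatever happened to the people who were lost. Since the article states a population and names it, this is not a detail left to the analysis plan.

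**Working it through.** **Step 1. Who is in the set.** The wording allows two readings. A: an assessment of the primary outcome means the week-16 value, the only one the article defines. B: any post-baseline four-week diary period counts.

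| Randomised participant | Reading A | Reading B |
|---|---|---|
| No session received | out | out |
| At least one session, no post-baseline diary | out | out |
| At least one session, diary before week 16, lost by week 16 | out | in, status missing |
| Stopped sessions early but assessed at week 16 | in | in |
| Assessed at week 16, lost later | in, status known | in, status known |

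The first two rows are out on both readings, so neither is intention-to-treat. Under A, nobody in the set lacks week-16 status. Under B, the third row gives the missing-data rules cases to act on, but the first two rows never reach them.

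**Step 2. The plan's attrition figure.** The sample-size section gives 199 required, 10% attrition, 218 recruited and 109 per arm. 199 × 1.10 = 218.9, and 199 / 0.90 = 221.1 (222 rounded up). The stated 218 is close to both, so the attrition step reproduces. Nothing below depends on how 199 was obtained.

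**Step 3. Illustration for Reading A.** The document gives n = 109 per arm, 10% attrition, and responder proportions of 46% and 35% (a previous study cited in the sample-size section). I assume that all attrition falls before week 16 and equally in both arms, that 46% and 35% apply to those assessed, and that week-16 status is either fully known or fully absent.

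Lost per arm: m = 109 × 0.10 = 10.9, about 11. Assessed: k = 109 - 11 = 98. Analysed: 196 of 218, with 22 excluded.

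With d = 0.46 - 0.35 = 0.11:

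- Literal set, under any of the rules: d = +11.0 points, since no status is missing.
- All randomised, missing as nonresponse: k·d / n = 10.78 / 109 = +9.9 points.
- All randomised, worst case: (k·d - m) / n = (10.78 - 11) / 109 = -0.2 points. By arm: 45.08 / 109 = 41.36% and (34.30 + 11) / 109 = 41.56%.
- All randomised, best case: (k·d + m) / n = 21.78 / 109 = +20.0 points.

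The same formulas at other losses before week 16:

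| Loss | m | k | Literal set | Nonresponse | Worst case | Best case |
|---|---|---|---|---|---|---|
| 5% | 5 | 104 | +11.0 | +10.5 | +5.9 | +15.1 |
| 10% | 11 | 98 | +11.0 | +9.9 | -0.2 | +20.0 |
| 20% | 22 | 87 | +11.0 | +8.8 | -11.4 | +29.0 |

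**Step 4. Reading B.** The article does not say how many participants might have no session or no post-baseline diary, so the number excluded cannot be computed.

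**Step 5. The two primary rules.** For a participant who met the responder threshold at week 12 and was lost before week 16, the Primary outcome section gives nonresponder. LOCF on responder status gives responder. The article therefore has no single primary rule.

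**The case against.** A reader might infer that the primary set is a completers set, that the missing-data rules act on nobody, and that the effect would vanish once lost participants are counted. The document does not support going that far.

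Several features point to Reading B. The definition asks for one assessment or more, which is odd for an outcome measured once. LOCF needs earlier values. A random-intercept model suggests repeated measurements. The per-protocol set separately requires assessment at weeks 8 and 16, and the week-16 part would be redundant under Reading A. The sample-size section lists assessment intervals among its model variables. Headache days, the raw data for response, are collected every four weeks. On that reading the set is a modified intention-to-treat set and the rules have cases. Even under Reading A, completers is too strong a word, because people who stop sessions but are assessed at week 16 stay in. Multiple imputation of the secondary outcomes would also still have work to do.

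The figure of -0.2 is a deliberate extreme, not an estimate of bias. It needs all 10% attrition to fall before week 16, although half of the 32 weeks after randomisation come later and the Discussion links dropout to the long observation period. There are also protections: randomisation is central, participants and assessors are blinded, and acupuncturists do not assess outcomes. Differential early loss is possible, not shown.

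All of that stands, and it limits the size of the problem. It does not remove it. Reading B still excludes randomised participants on post-randomisation grounds, and the article defines response only at week 16, so it does not settle which reading applies.

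**Conclusion.** The point holds in this form. The set is mislabelled on either reading, and its wording conflicts with the single week-16 outcome and the rules for missing primary data. Confidence is high on the label and the conflict. Which reading was meant is open.

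The size depends on the reading. Under the literal one, with the assumptions of Step 3, 22 participants is the upper end at 10% attrition, because losses after week 16 would exclude fewer. The planned scenarios would then all show +11.0 points, where the full randomised set gives a range from -0.2 to +20.0. At 5% loss before week 16 that range is +5.9 to +15.1. Under the wider reading the effect is probably smaller, but the document gives no basis for a figure.

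**What to change.** 1. Define the primary set as all randomised participants in their assigned arm, whether or not they received a session or have week-16 data.
2. Choose one primary rule for missing week-16 status. One option is nonresponse, as in the outcome definition, with LOCF as a sensitivity analysis. The present third scenario would then duplicate the primary analysis, and LOCF could take its place. If LOCF is used at all, say what is carried forward for a participant with no post-baseline diary.
3. Run the best-case and worst-case scenarios on the full randomised set.
4. State that participants removed under the Dropout criteria stay in the analysis set.
5. If the present definition is still wanted, keep it as a secondary modified intention-to-treat set, and say whether its assessment condition means week 16 or any post-baseline diary period.

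This means short edits to the Primary outcome, Dropout criteria and Statistical analysis sections, with no new data collection. It should be settled before unblinding; the article reports recruitment as under way. The downside is slight dilution of the estimate: in the illustration, from +11.0 to +9.9 points under the nonresponse rule.

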## Method and design

### Study design

This study is a parallel-design, patient-assessor blind RCT comparing an acupuncture treatment group with a superficial acupuncture control group. Two hundred and eighteen patients with CTTH will be recruited through but not limited to: reviewing and screening of outpatients in the Teaching Hospital of Chengdu University of Traditional Chinese Medicine, university media releases, community advertisement including distributing leaflets via regular community health counselling, media campaigns, and network recruitment.

Eligible participants will be randomly assigned to the acupuncture treatment group or the superficial acupuncture control group with a 1:1 ratio. The total observation period will be 36 weeks, including a 4-week baseline period, an 8-week treatment period and a 24-week follow-up period. They will receive 20 sessions of acupuncture or superficial acupuncture treatment over 8 weeks (three sessions per week in the first 4 weeks and two sessions per week in the following 4 weeks). During the baseline, treatment and follow-up periods, participants will not be allowed to take any prophylactic medications (e.g., amitriptyline, clomipramine, and mirtazapine) for CTTH, but will be permitted to use necessary analgesics (e.g., ibuprofen, paracetamol and ibuprofen) when headache is unbearable The type, dose and time of administration will be recorded in headache diaries. Assessments will be conducted at baseline and at 4, 8, 12, 16, 20, 24, 28, 32, and 36 weeks after randomization. Figures 1 and 2 illustrate the time schedule of enrolment, interventions, assessments, and visits of participants. The reporting of this trial is conducted according to the Standard Protocol Items: Recommendations for Intervention Trials (SPIRIT) guidelines (Additional file 1).

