### Participants

#### Study population and sample size

We will recruit CTTH sufferers who meet the diagnostic criteria in the International Classification of Headache Disorders, 3rd Edition (ICHD-3) formulated by the International Headache Society [1]. According to a previous study [11], the proportion of responders (at least 50% reduction in days with headache) was 46% after acupuncture treatment versus 35% after superficial acupuncture (odds ratio, 1.32). In this study, we expect an odds ratio of 1.35 when acupuncture is compared with superficial acupuncture. Assuming a significance level of 0.05, a study power of 0.8, and a correlation of 0.5 between independent variables (including study groups, assessment intervals, and the number of headache days at baseline), 199 participants are required to reject the hypothesis that acupuncture is equivalent to superficial acupuncture. Taking a 10% attrition bias into consideration, we will recruit 218 participants in total, with 109 in each group.

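### The primary logistic model places treatment allocation in its random part, so it has no treatment coefficient and cannot directly give the between-arm odds ratio, confidence interval or test that the protocol promises

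*Protocol article*

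**What the plan says.** The Statistical analysis section prescribes for the primary outcome a "random intercept logistic regression model, taking treatment allocation as a random factor and taking sex, age, and duration of headache as fixed factors". That sentence sorts the terms into two parts: treatment is random, and three baseline variables are fixed. No other part of the article gives treatment a fixed effect for this outcome or names another unit for the random intercept.

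The same section then states: "All confidence intervals will be two-sided 95% intervals comparing acupuncture to superficial acupuncture and all statistical hypotheses will be two-sided tests". Participants are "randomly assigned to the acupuncture treatment group or the superficial acupuncture control group with a 1:1 ratio", so the factor has two levels. The Primary outcome section sets one time point: "The primary outcome measurement is the proportion of responders at week 16".

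The sample-size section plans on an odds ratio of 1.35 and assumes a "correlation of 0.5 between independent variables (including study groups, assessment intervals, and the number of headache days at baseline"). That list differs from the one in the analysis section, which has neither assessment interval nor baseline headache days.

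Headache days, intensity, SF-36, HAMA and HAMD are to be "analyzed using a generalized least squares regression model, with the same covariates as the primary outcome".

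**The concern.** A random factor suits levels that are a sample from a wider population whose spread is of interest. Here the two arms are themselves the comparison. Once treatment is random, the parameter attached to it is a variance estimated from two groups. The odds ratio on which the trial is planned is not a parameter of the model, and the promised interval for the arm comparison has nothing to attach to.

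At stake is the primary result. An analyst who follows the sentence gets a predicted arm difference that is systematically too small and often exactly zero. An analyst who departs from it must choose, possibly after seeing data, between a week-16 logistic regression and a longitudinal model. Prespecification is meant to remove that choice.

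**Working it through.** **The plan's own figures.** The sample-size section cites "46% after acupuncture treatment versus 35% after superficial acupuncture (odds ratio, 1.32"). The rates give an odds ratio of (0.46/0.54)/(0.35/0.65) = 1.58; the risk ratio is 0.46/0.35 = 1.31. The printed 1.32 is therefore not reproduced as an odds ratio. That is a separate matter, and nothing below depends on it or on the stated total of 199.

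**Inputs.** 109 per arm (sample-size section). 38/109 = 34.9% in the control arm, close to the cited 35%. For acupuncture: 50/109 = 45.9% (the cited 46%), 46/109 = 42.2% (close to the planned odds ratio of 1.35), and 54/109 = 49.5% (a larger effect). Covariates are left out, and every participant is counted.

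**Treatment fixed.** With a and c responders, d = ln[a/(109−a)] − ln[c/(109−c)] and SE² = 1/a + 1/(109−a) + 1/c + 1/(109−c).

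- 50 v 38: d = 0.460, SE = 0.278, z = 1.65; OR 1.58 (0.92 to 2.73), p = 0.098.
- 46 v 38: d = 0.311, SE = 0.279, z = 1.11; OR 1.36 (0.79 to 2.36), p = 0.27.
- 54 v 38: d = 0.607, SE = 0.278, z = 2.19; OR 1.83 (1.07 to 3.16), p = 0.029.

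**Treatment random.** A normal approximation shows the mechanism. Let v = SE²/2 be the sampling variance per arm. The maximum-likelihood (ML) arm variance is s² = max(0, d²/4 − v), and the predicted arm difference is d × s²/(s² + v).

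- 50 v 38: v = 0.0387, d²/4 = 0.0528, s² = 0.0141 (SD 0.12). Shrinkage factor 0.0141/0.0528 = 0.27; exp(0.27 × 0.460) = 1.13.
- 46 v 38: d²/4 = 0.0241 is below v = 0.0390, so s² = 0 and the predicted odds ratio is exactly 1.00.
- 54 v 38: v = 0.0386, d²/4 = 0.0920, s² = 0.0535. Factor 0.58; exp(0.58 × 0.607) = 1.42.

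A full ML fit of the logistic model by numerical integration gives 1.13, 1.00 and 1.43.

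Since d²/4 < v is the same as z² < 2, the ML variance is zero whenever |z| < 1.41.

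**The test that remains.** A likelihood-ratio test of the arm variance is possible, with half the chi-square(1) tail as its p-value because zero is on the boundary. For 54 v 38 the statistic is 1.07, giving p = 0.15 against 0.029 with treatment fixed. In the approximation the statistic equals z² − 2 − 2 ln(z²/2) for z² > 2. It passes the 5% critical value of 2.706 only when |z| exceeds about 2.70, against 1.96 for the fixed-effect test.

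**Long-run behaviour** (400,000 draws under the same approximation):

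| Truth | Variance zero, ML | Variance zero, REML | Variance test rejects (ML) | Fixed-effect test rejects |
|---|---|---|---|---|
| 46% v 35% | 40% | 25% | 15% | 38% |
| OR 1.35 | 62% | 45% | 5% | 19% |
| No difference | 84% | 68% | 0.7% | 5% |

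At 46% v 35% the mean predicted log odds ratio is 0.23 (ML) or 0.32 (REML), against a true 0.46.

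**Where the effect is weaker.** At 60 v 38 the full ML fit gives 1.90 against a fixed-effect 2.29, and the variance test is significant (p = 0.022). At 65 v 38 it gives 2.37 against 2.76. Under REML, s² = max(0, d²/2 − v); at 50 v 38 this is 0.1056 − 0.0387 = 0.0669, the factor is 0.0669/0.1056 = 0.63, and the predicted odds ratio is exp(0.63 × 0.460) = 1.34.

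**The case against.** The strongest reply is that the sentence is a slip for a fixed treatment effect with a random intercept for participant. The promised arm-comparing intervals and the planned odds ratio both point that way. The slip is plausible, but it does not make the stated model right. Treatment is named as random in so many words, and the participant is not named at all. Nor is this detail left to an analysis plan: the article states the model and states it wrongly.

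A reader might infer more than the document supports, in four ways.

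- *That no test or odds ratio can be obtained at all.* The arm variance can be tested, and an odds ratio can be formed from the predicted arm effects. But the test has no direction and is very conservative, and the odds ratio is shrunken.
- *That a participant intercept could not be identified.* This is true if only one binary value per participant is analysed, as "This outcome measurement will be assessed at week 16 after randomization" suggests. However, the sample-size text lists assessment intervals, assessments are four-weekly, the intention-to-treat set requires at least one primary-outcome assessment, and the per-protocol set requires weeks 8 and 16. If responder status at repeated visits is modelled, the intercept is identifiable.
- *That the secondary models also treat allocation as random.* Sharing covariates most naturally refers to sex, age and duration. The role of treatment there is unclear, not established as random.
- *That the shrinkage is always severe.* The figures are unadjusted and mostly ML, and shrinkage lessens with larger effects or REML.

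**Conclusion.** The primary model is wrong as written and contradicts the inference promised in its own section. Taken literally, it offers a two-level variance and shrunken predictions in place of the week-16 odds ratio with its interval and two-sided test. Around the planned effect the consequence is material: a fixed-effect odds ratio of 1.58 becomes 1.13, one of 1.36 becomes 1.00, and a result with p = 0.029 becomes non-significant at about 0.15.

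These sizes assume 109 analysed per arm, no covariates and maximum likelihood. The absence of a treatment coefficient does not depend on those assumptions. The error lies in the stated analysis, not in the trial's design or data, but it concerns the primary comparison and must be corrected before analysis.

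**What to change.** Enter treatment as a fixed effect, together with the prespecified covariates, and report the week-16 odds ratio of acupuncture against superficial acupuncture with its two-sided 95% interval. Then state which of two models is meant:

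1. Week 16 only: ordinary logistic regression, with the random intercept dropped.
2. Repeated visits: a random intercept with participant named as its unit; fixed treatment, visit and treatment-by-visit terms; and the week-16 contrast named as primary. Without the interaction, the treatment term would be an average over visits, not the week-16 effect.

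State also that treatment is a fixed effect in the generalized least squares models for the secondary outcomes.

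The cost is a change of wording in the analysis section, made before data are analysed by arm. No data collection, sample size or participant is affected.
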